### Sample and Recruitment Strategies

This pilot study acknowledges the potential for selection bias because individuals who volunteer for this PA-related study may already have a relatively high level of motivation to change their behavior. According to a priori power analysis using G*Power 3.1 [26], considering an α level of .05, an estimated effect size (f) of 0.2, an anticipated correlation of 0.4 among repeated measures, and 4 measurement levels of within-subjects factors, we project a total sample of 55 autistic adults to achieve a power of 0.9. To be eligible, prospective participants must (1) be adults aged 18 years to 55 years, (2) have received a formal diagnosis of ASD from a qualified medical professional, and (3) own and regularly use a compatible iPhone (iOS 14+ operating system). Android version development is underway, and its users will be invited to participate in future clinical trials. Individuals with moderate-to-profound intellectual disability or orthopedic conditions that significantly interfere with independent information processing or ambulation (eg, using a wheelchair or crutches) will be excluded from the study. These individuals may encounter challenges in engaging with the cognitive and physical aspects of the intervention, such as understanding verbal or written instructions, independently using the app, or meeting study requirements (eg, returning study materials to the research team). Therefore, only individuals who live semi-independently or independently, have autonomy for daily living, and are capable of making their own research-related decisions will be given an informed consent form to sign and subsequently invited to participate in the study. Future research shall explore adaptation strategies to make the mHealth interventions more accessible to a broader autistic population, including those with co-occurring moderate-to-profound intellectual disability.

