### PuzzleWalk mHealth System

PuzzleWalk is a gamified, behavior change theory–guided mobile app designed to promote regular PA participation among autistic adults by leveraging practical behavior change techniques and principles of self-determination theory [12,20,28]. Key innovative features include a step-to-game conversion algorithm, which translates users’ daily step counts into time for solving image-based puzzle games, highlighting iconic cityscapes from around the world. This user-centered design builds on the strengths of autistic individuals in visual learning and fosters intrinsic motivation through autonomy, relatedness, and competence. To achieve these core elements of self-determination theory, PuzzleWalk incorporates self-monitoring of step counts to support autonomous app engagement, visual puzzle games, contingent rewards to enhance competence, and a competition-based leaderboard and shared goals to foster relatedness among autistic users. PuzzleWalk v2 builds on the original version through iterative design enhancements guided by feedback from key stakeholders during the participatory workshop phase. A major advancement in PuzzleWalk v2 is the inclusion of improved accessibility features, such as step-by-step visual guides, simplified interface navigation, and animated icons and buttons to enhance user-friendliness. Another key improvement from v1 to v2 is the introduction of a gamified goal-tracking feature that uses a quest-based design, allowing users to unlock puzzle rewards by reaching step count milestones (Figure 2). The leaderboard scores are determined by combining accumulated step counts and puzzle points. Top scorers on the leaderboard are eligible to receive tangible incentives (eg, Amazon e-gift cards) at the end of each month. Importantly, the PuzzleWalk system automatically resets leaderboard scores at the end of each month to encourage consistent PA engagement among users. Detailed descriptions of the PuzzleWalk v1 system can be found in previous studies [20,28].

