**App Engagement Assessment**

The level of user engagement in the PuzzleWalk intervention will be measured through a Laravel-based backend system, which uses the Voyager administration system for data visualization and management (eg, frequency and duration of app use, step counts, and puzzle points). Time spent on the app in a minutes-per-day format will be calculated to represent each participant’s level of user engagement. These app engagement metrics will be aligned with accelerometer-derived PA and sedentary time to explore how engagement levels relate to daily behavior patterns. Although the study does not include a control group, a 7-day baseline measure will enable within-subject comparison over time. Additional sensitivity analyses will examine how variations in app engagement influence behavioral outcomes during the intervention period. Only activities related to the PuzzleWalk app will be accessed by the software developer and corresponding author as a principal investigator. Any identifiable information, such as email address, will be destroyed immediately upon completion of data collection to ensure participant confidentiality. Follow-up interviews will be conducted after the intervention ends to explore participants’ perceived acceptability, individual experiences (eg, satisfaction challenges), and factors that may have contributed to (dis-)continuation of the app use during and beyond the study. To secure and facilitate dataflow in the PuzzleWalk system, the user authentication process using Apple ID (ie, account credentials) will involve several key steps. First, the user initiates authentication through their Apple ID on the PuzzleWalk app. The app then obtains an authentication token from Apple, and forwards it to the backend server for verification with Apple’s authentication system. Once the token is verified, the backend server generates a session token, enabling the app to access the server application programming interface (API). This session token will facilitate secure API communication, allowing the backend server to interact with the database in real time and manage user requests efficiently (see Figure 3).

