### Data Analysis

Accelerometry data will be systematically analyzed by inspecting ranges and addressing missing values in accordance with the previously outlined validation protocol. The raw accelerometry output will be transformed into CPM values and processed using ActiLife software (ActiGraph). To account for the typical lifespan of mHealth interventions (eg, ≤3 months) [35], an intention-to-treat approach will be applied to ensure external validity. Baseline comparisons between autistic adults with and without mild intellectual disability, as well as between male and female autistic adults, will be conducted using independent *t* tests and chi-square tests. We will perform repeated measures ANCOVA to examine the changes in participants’ objective levels of PA and sedentary time before, during, and after the 6-week intervention, adjusting for baseline characteristics, including age, sex, mild intellectual disability, and BMI. Bonferroni post hoc tests will be performed if a significant difference is found between time points. Dependent variables will include light PA, MVPA, sedentary time (minutes per day), MVPA in bouts of >10 minutes per day, steps per day, and user engagement (eg, number of app login sessions and time spent on app use per day). Independent variables will be each time point and intervention. Pearson correlation analyses will be used to examine the relationship between the levels of PA, sedentary time, and user engagement during the intervention period. We will perform data analyses using SPSS v29 (IBM Corp), and the significance level will be set at *P*<.05 (2-tailed).

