## Discussion

This paper outlines the research protocol for developing and field-testing PuzzleWalk v2, a novel mHealth system designed to promote regular PA and reduce SB in autistic adults with and without mild intellectual disability. The system uses gamification and evidence-based behavior change strategies developed with key autism stakeholders. The protocol establishes a structured methodology for the co-design process and remote deployment of a gamified mHealth intervention that can be scalable in real-world settings. By incorporating community input into the app’s refinement and using replicable, remote data collection methods, this study is positioned to yield critical insights into behavior change strategies and underlying mechanisms among autistic adults. The detailed procedures and supporting resources provided in this paper lay a strong foundation for future evaluation and broader dissemination of tailored digital health interventions for individuals with ASD. It is anticipated that high user engagement with PuzzleWalk v2 will be associated with increased MVPA, higher step counts, and reduced sedentary time among participants with ASD in Phase II.

It is important to note that the vast majority of autism research has focused on understanding the pathology, etiology, and symptoms of this condition with little attention to helping autistic adults live healthy lifestyles [36]. There are limited data on the preventive health behaviors of autistic adults measured by objective and reliable wearable devices in a real-world context [11]. Previous findings on objectively measured PA and SB in individuals with autism have been interpreted with caution because of the small sample sizes with moderate-to-low statistical power [11]. Due to the lack of dedicated surveillance systems, autistic adults who live semi-independently, with and without mild intellectual disability, have not been precisely monitored, as they are mostly not affiliated with community organizations or public school systems [3]. Identifying effective recruitment strategies to upscale the sample size and verifying the feasibility of remote intervention delivery methods are major strengths of this protocol.

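### The planned correlation between activity and app engagement is confounded, because steps earn app time and no baseline adjustment is stated

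*Protocol article*

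**What the plan says.** - **Protocol article, PuzzleWalk mHealth System:** the conversion algorithm turns "daily step counts into time for solving image-based puzzle games". Version 2 also unlocks puzzle rewards at step milestones. The conversion rate is not given.
- **App Engagement Assessment:** the backend handles, as examples, "frequency and duration of app use, step counts, and puzzle points". The measure then chosen to represent engagement is minutes per day on the app. Engagement is to be aligned with accelerometer-derived activity in an exploratory way. Additional sensitivity analyses are to look at how variation in engagement may *influence* behaviour.
- **Data Analysis:** engagement is exemplified by login sessions and time on the app. "Pearson correlation analyses will be used to examine the relationship between the levels of PA, sedentary time, and user engagement during the intervention period". Age, sex, mild intellectual disability and BMI are covariates of the repeated measures ANCOVA. No adjustment is stated for the correlations.
- **Discussion:** the authors anticipate that "high user engagement with PuzzleWalk v2 will be associated with increased MVPA, higher step counts, and reduced sedentary time". This is the only explicit directional expectation for Phase II.

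**The concern.** Two features of the plan work together.

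1. *Reverse dependence.* More steps earn more permitted puzzle time, so app minutes are partly a consequence of the activity they are meant to explain.
2. *Levels instead of change.* The expectation concerns increased activity, but the correlation relates levels within the intervention period. A person who walked a lot before the app arrived, and walks the same amount afterwards, can contribute high steps and high app minutes.

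The trial has one arm, so a gradient of activity with engagement is an obvious candidate for evidence that the app works. As planned, a positive gradient cannot separate the app raising activity from activity unlocking the app.

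**Working it through.** **1. The plan's own sample-size figure.** Inputs from Sample and Recruitment Strategies: α = 0.05, f = 0.2, ρ = 0.4 and m = 4. For one group with a within-subjects factor, λ = f²·N·m/(1−ρ), df1 = m−1, df2 = (N−1)(m−1).

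At N = 55: λ = 0.04 × 55 × 4 / 0.6 = 14.67, with 3 and 162 df. Power is 0.903 (0.897 at N = 54). The stated 55 reproduces, and power at 70 is 0.962. This N is for the effect of time; no figure is stated for the correlation.

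**2. Threshold for the correlation.** Critical |r| = t/√(N−2+t²), two-sided 0.05. It is 0.266 at N = 55 and 0.235 at N = 70.

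**3. No app effect, earned time acts as a cap.** App minutes = min(desired minutes, conversion rate × steps). Assumptions not in the article: steps about normal with mean 7000 and SD 2800; desired minutes log-normal (log SD 1) and independent of steps; median desired time 2 to 20 minutes a day; conversion 0.5 to 5 minutes per 1000 steps; 4000 simulated trials per scenario.

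| Participants limited by earned time | Mean r, steps with app minutes | Significant positive, N = 55 | Significant positive, N = 70 |
|---|---|---|---|
| no conversion | 0.00 | not run | 2% |
| 1% | 0.01–0.02 | 2% | 3% |
| 5% | 0.07 | 6% | 7% |
| 15% | 0.17 | 21–23% | 28–29% |
| 20% | 0.21–0.22 | 34% | 45% |
| 33% | 0.33–0.34 | 71–73% | 82% |
| 41% | 0.40 | 86% | 93% |
| 65% or more | 0.64 or more | about 100% | about 100% |

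The nominal upper tail is 2.5%.

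**4. No app effect, people use a fraction of what they earn.** With a random (Beta) fraction independent of steps, r is 0.32 to 0.81 and is significant in 80% to 100% of trials at N = 70. A closed form gives the same picture. If minutes = earned time × an independent uptake factor, r = c/√(c²+u²+c²u²), where c and u are the coefficients of variation of steps and uptake. With assumed c = 2500/7000 = 0.357, r is 0.75 at u = 0.3 and 0.22 at u = 1.5. The chance of significance at N = 55 is then 100% and 36%.

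**5. Sedentary time.** If app time relates to sedentary time only through steps, the implied r is the product of the two correlations. Assumed extremes: −0.3 × 0.3 = −0.09 and −0.7 × 0.7 = −0.49. The chance of significance at N = 70, by Fisher z, is 11% and 99%.

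**6. Would baseline adjustment alone be enough?** Suppose minutes depend on week 1 steps only through current steps. The partial correlation is then r√(1−ρ²)/√(1−r²ρ²). With the plan's ρ = 0.4 and r = 0.40: 0.40 × 0.917/√(1 − 0.16 × 0.16) = 0.367/0.987 = 0.37. At that ρ, adjustment barely reduces the part due to the conversion. The engagement measure has to change as well.

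**The case against.** - *The point concerns a side analysis.* This stands. The stated aims are feasibility and acceptability, the expectation is one sentence in the Discussion, and the analysis that was sized is the time effect. A reader might infer that the trial's main hypothesis is circular. The article does not support that: change over time is tested by repeated measures ANCOVA, which the conversion does not disturb when activity or sedentary time is the outcome.
- *Steps are not the engagement score.* This mostly stands. A reader might infer from the backend list that steps would be correlated with themselves. But that list can be read as what the system handles, the named measures are minutes and logins, and activity comes from the accelerometer. Literal overlap arises only if app steps or puzzle points are used as the score, which the text neither states nor rules out.
- *The association need not appear.* This stands. A reader might infer that the expectation is bound to be confirmed. The rate depends on how often earned time limits use, which is unknown. Other app functions (step self-monitoring, leaderboard) are not said to cost earned time. Two of five testers found the puzzles too challenging, so difficulty may limit play as well. Logins are not shown to be limited by steps. Seated puzzle play could work against the sedentary-time part.
- *The wording is mostly associational.* This is true apart from the verb *influence* for the sensitivity analyses, whose method the article does not give; they cannot be judged further. Exploratory wording does not make a reverse-dependent correlation interpretable.

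**Conclusion.** The concern holds for the unadjusted correlation of levels when app minutes measure engagement. Reverse dependence and stable differences between people could produce the anticipated positive association with no app effect, so a positive result is not by itself support for the expectation in the Discussion.

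The size cannot be fixed from the article. For steps at N = 70 the false-positive rate runs from near nominal (3%), if earned time seldom limits use, to about 100%, if it limits most participants. All of these rates rest on assumed step counts, desired play time and conversion rates. The steps part is the most exposed; MVPA was not simulated, and the sedentary-time part is less certain. The sample size and the ANCOVA on activity outcomes stand.

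**What to change.** Before the data are analysed:

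1. Replace the unadjusted correlation of levels with a regression, or partial correlation, of activity in weeks 3, 5 and 8 on engagement, adjusted for the participant's week 1 value of the same outcome.
2. Make logins or the share of earned time used the main engagement measure, with raw app minutes secondary. Logins are the simpler choice: the share has steps in its denominator and can lean the other way if people want a fixed amount of play.
3. State that app step counts and puzzle points are not used as the engagement score.
4. Describe the result as association, and replace *influence* in App Engagement Assessment.

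A within-person daily model is optional. A previous-day lag might miss a same-day sequence of walking and then playing.

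The cost is a few sentences and slightly more analysis work. Week 1 accelerometry, logins and app minutes are already planned; the share of earned time also needs the app's conversion rule. The correlation reported will probably be smaller.

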## Results

Phase I of the project, community-based participatory design workshops (n=9; 4/9, 44% women) was recently concluded. The findings revealed that key autism stakeholders highly valued the app’s self-monitoring and step tracking feature, leaderboard, and visual design. These features were perceived to enhance their perceived motivation for PA engagement and fostered a sense of friendly competition among users. Most stakeholders indicated that the app helped increase PA, reduce SB, and provide a sense of achievement. Autistic traits such as perfectionism and competitiveness reportedly influenced the level of engagement, sometimes enhancing motivation but occasionally causing discouragement due to the difficulty of the puzzle games. Overall, the app was viewed as a potentially beneficial tool for promoting PA and reducing SB in autistic adults (see Table 2). Data collection for Phase II of the project, which involves field deployment (approximate n=70), is currently underway and is expected to be completed in August 2025. As of July 2025, we enrolled 69 participants in the study. The results of this study will be shared in a subsequent publication.

**Table 2 table2:** Key findings of community-based participatory design workshops.

Activities	Key findings
Screening interviews and general inquiry on demographics, patterns of PA^a^ and SB^b^, and overall health among community stakeholders with autism	Most autistic collaborators were diagnosed with ASD^c^ during their early childhood by a medical professional and preferred communication via text messaging or email. Walking was the most preferred form of PA participation among collaborators with autism, but its frequency varied from “rarely” to “four times a week.”
Exploration of preferences and patterns of general technology use and its influence on PA and SB among autistic adults	Health-related mobile apps were generally seen as frustrating or unengaging due to complex interfaces or a lack of engaging features. Feedback highlighted the need for more intuitive functionality and fewer notifications. When it comes to gaming mobile apps, collaborators with autism tended to prefer simple or classic games rather than complex or time-intensive ones. Most collaborators with autism used their smartphones at home or work and typically kept them in a pocket when walking.
Identification of factors influencing PA participation and perceived health benefits of PA	Motivation factors for PA among collaborators with autism varied, ranging from social support provided by family members or therapists to using PA as a means to reduce stress and anxiety. Perceived barriers included low stamina, preference for sedentary activities (eg, watching TV or using social media), and mental health challenges or overthinking. Most collaborators acknowledged the health benefits of PA, particularly its positive effects on physical and mental well-being, as most indicated that they felt happier, healthier, and more fulfilled after engaging in PA.
Evaluation of the core features and identification of areas for improvement in PuzzleWalk v1	Several collaborators suggested adding more puzzle levels and variety to keep the app more engaging. Overall concept (eg, taking steps to play puzzle games) and competitive aspects of the app (eg, leaderboard) were viewed as strengths. Few collaborators recommended incorporating quest-based milestones for unlocking puzzles and intuitive reward systems to motivate continued PA engagement.
Autism-friendly intervention design and pilot compatibility and functionality testing of PuzzleWalk v2 in real-world settings	All 5 collaborators who owned an iPhone during the study successfully installed and tested the app on their devices without any functional issues. Although collaborators appreciated the reward-based system, leaderboard, and step tracking features, 2 of them found the puzzles too challenging, which reduced their perceived enjoyment and continuation desire. According to user feedback, collaborators felt the app effectively promoted self-monitoring of PA and provided a sense of community (eg, competing with other autistic users on the leaderboard) and motivation to be more active during the testing period.

^a^PA: physical activity.

^b^SB: sedentary behavior.

^c^ASD: autism spectrum disorder.

## Discussion

This paper outlines the research protocol for developing and field-testing PuzzleWalk v2, a novel mHealth system designed to promote regular PA and reduce SB in autistic adults with and without mild intellectual disability. The system uses gamification and evidence-based behavior change strategies developed with key autism stakeholders. The protocol establishes a structured methodology for the co-design process and remote deployment of a gamified mHealth intervention that can be scalable in real-world settings. By incorporating community input into the app’s refinement and using replicable, remote data collection methods, this study is positioned to yield critical insights into behavior change strategies and underlying mechanisms among autistic adults. The detailed procedures and supporting resources provided in this paper lay a strong foundation for future evaluation and broader dissemination of tailored digital health interventions for individuals with ASD. It is anticipated that high user engagement with PuzzleWalk v2 will be associated with increased MVPA, higher step counts, and reduced sedentary time among participants with ASD in Phase II.

It is important to note that the vast majority of autism research has focused on understanding the pathology, etiology, and symptoms of this condition with little attention to helping autistic adults live healthy lifestyles [36]. There are limited data on the preventive health behaviors of autistic adults measured by objective and reliable wearable devices in a real-world context [11]. Previous findings on objectively measured PA and SB in individuals with autism have been interpreted with caution because of the small sample sizes with moderate-to-low statistical power [11]. Due to the lack of dedicated surveillance systems, autistic adults who live semi-independently, with and without mild intellectual disability, have not been precisely monitored, as they are mostly not affiliated with community organizations or public school systems [3]. Identifying effective recruitment strategies to upscale the sample size and verifying the feasibility of remote intervention delivery methods are major strengths of this protocol.

Given the prevalent social and sensory challenges, traditional face-to-face PA interventions in community-based public settings may not be a sustainable behavior change model nor an effective strategy for autistic adults [37,38]. Due to the complexities of the intervention delivery and assessment protocols, the existing evidence is insufficient to confirm that traditional exercise interventions lead to long-term improvements in PA levels in this population [11]. Although the benefits of regular, face-to-face PA participation are well-documented, it is critical for researchers, educators, and service providers to diversify the PA options for autistic adults by creating environments that are inclusive, relevant, and sensitive to their needs and preferences [15,39]. While mobile technology research has made significant progress in improving the life skills of autistic individuals (eg, social and communication skills) [40], only a few technological attempts have been made to address PA engagement issues in this population. Gamification strategies have emerged as a viable approach for enhancing PA levels and reducing sitting time, especially in those with low intrinsic motivation for voluntary behavior changes [19,41]. However, research on the practicality of this gamification approach in mHealth interventions remains in its early stages and is not yet fully understood for autistic adults, who may have unique preferences, motivational factors, and barriers to behavior change [15]. In addition, mHealth-guided behavior change interventions generally result in only short-term participant engagement [42]. Rigorous empirical research is essential to develop replicable and comprehensive interventions grounded in evidence-based frameworks and to promote sustainable PA behavior changes for autistic adults [15].

Historically, autism research has often misrepresented the autism community by excluding individuals with ASD from the research process, using outdated or stigmatizing language, and prioritizing research agendas that may not align with autism community values [25,43]. In response to the increasing demand for collaborative autism health research, this study used community-based workshops to identify achievable strategies for mHealth-guided PA and SB changes. Subsequently, these workshops also informed the gamification design aesthetics for tailoring the intervention to the needs of autistic adults. To establish alignment between the research team and key autism stakeholders, we leveraged the practical guidelines for collaborative autism research, informed by AASPIRE [25]. The results of the field deployment study (Phase II) will be shared with the workshop participants, and their additional input will be sought to refine the intervention protocol for future clinical trials with a control group (eg, longitudinal randomized controlled trials).

A limitation of this study is the restriction of eligibility to iPhone users, which may introduce sampling bias. Although an Android version of the app is currently in development, this criterion may exclude individuals who cannot afford iPhones or prefer Android devices. Consequently, a significant portion of autistic adults, particularly those with financial constraints or differing technology preferences, may be underrepresented. Therefore, future work should focus on expanding and evaluating PuzzleWalk v2 across a wide range of smartphone brands and models to enhance accessibility and scalability. Given that individuals who choose to participate in this game-oriented mHealth study may have a greater interest in or familiarity with mobile gaming, the use of a robust recruitment strategy and inclusion of a diverse and adequately powered sample are expected to reduce sampling bias and to enhance the generalizability of the findings. Study results will be disseminated through various channels, including scholarly conference presentations and peer-reviewed publications. Furthermore, findings from this study will guide the continued refinement of the PuzzleWalk system, with the long-term goal of facilitating its future public release and broader implementation. Future research should also explore the influence of community-level factors on the successful implementation of PA intervention strategies. Given the importance of ecological validity in PA research [44], community-level factors, including associability and affordability of community resources, social support networks, and environmental conditions that facilitate PA participation, should be considered in designing and evaluating PA interventions for autistic adults.

